## Methods

### Study Design and Setting

This is a community-partnered, 2-arm cluster-RCT to evaluate FHF in 16 neighborhoods (clusters) across Pittsburgh, Pennsylvania, and the Washington, DC, metro area (Figure 1). Neighborhoods are the unit of randomization to minimize contamination and align with community delivery. Approximately 45 youth (aged 13‐19 y) will be enrolled per neighborhood (target N≈720). Assessments occur at baseline (T1), end-of-program (6‐12 wk after baseline), 3 months (T2), and 6 months (T3) postprogram. A mixed methods design integrates quantitative surveys with qualitative interviews and implementation tracking aligned with the RE-AIM (reach, effectiveness, adoption, implementation, and maintenance) framework, enabling rigorous effectiveness testing alongside implementation evaluation.

**Figure 1. F1:**
[figure not shown]
Two-arm cluster–randomized controlled trial study flow. DMV: Washington, DC, and Maryland metro areas.

### Participants and Recruitment

Eligible participants are adolescents aged 13‐19 years who live, attend schools, or use participating facilities in a randomized neighborhood, can complete study procedures in English, and can provide follow-up contact information. Youth will be identified through community-based organizations, outreach by neighborhood facilitators, peer referrals, and partnerships with local health, social service, and youth development programs. After eligibility screening, informed consent or assent will be obtained in private settings. The study was approved by the University of Pittsburgh with a waiver of parental permission (for youth aged 13‐17 years) and a waiver of written documentation of consent.

### Randomization and Allocation Concealment

Th*e* trial design builds on primary prevention principles that emphasize a comprehensive, theory-driven approach, sufficient dosage (through repeated exposure to content), and youth participation balanced with the feasibility and cost of implementation approaches. Randomization is performed at the neighborhood level (ie, cluster) to reduce the risk of contamination. Neighborhoods are stratified by city (Pittsburgh vs Washington, DC, and Maryland metro areas [DMV]) and randomized 1:1 to FHF or enhanced usual care (wellness check-ins) by the study statistician using reproducible code. Randomization lists are generated prior to enrollment and implemented centrally; site teams will be notified of the assignment after cluster confirmation. Analyses will be conducted with masked arm labels, and outcome assessments will use standardized instruments to minimize bias.

### Intervention and Comparison Arms

FHF comprises 12 facilitated sessions (≈2 h each) delivered over 6 to 12 weeks in community settings by trained local facilitators. The program uses strength-based and healing-centered approaches to nurture youth leadership skills, promote healthy relationships, develop conflict resolution and upstander skills, and build job skills and employment readiness (Figure 2). Facilitators receive standardized training, ongoing coaching, and fidelity monitoring using session checklists and observation rubrics. Near program completion, youth meet workforce partners and mentors to support concrete next steps.

**Figure 2. F2:**
[figure not shown]
Conceptual model underlying Forging Hopeful Futures.

Guided by our previous work demonstrating the violence prevention effects of both skills-building curricula and job readiness training [34], FHF was developed to explore the impact of combining this content into a unified intervention. The FHF curriculum was adapted by the study team by integrating content from four existing curricula: Manhood 2.0 [40], Sisterhood 2.0 [41], Creating Peace [42], and job skills training [43]; new synergistic content was also added. Community partners from youth-serving organizations worked with the FHF investigative team to synergize these evidence-based interventions into the FHF curriculum (Table 1). Community facilitators helped develop the facilitator and youth curriculum guides. We pilot-tested the FHF curriculum in one neighborhood not involved in the RCT and made additional refinements.

**Table 1. T1:** Forging Hopeful Futures curriculum content.

Session topic	Curriculum sources	Session content
1. Exploring identity	Manhood 2.0, Sisterhood 2.0, and Creating Peace	Set goals, examine community norms, promote knowledge, and positive identity.
2. Understanding our emotions and experiences	Manhood 2.0, Sisterhood 2.0, and Creating Peace	Share experiences of violence, posttraumatic growth, and vicarious resilience.
3. Healthy relationships	Manhood 2.0, Sisterhood 2.0, and Creating Peace	Support discussions of healthy relationships, consent, and signs of abuse through interactive dialogue and scenarios
4. Examining history and power	Creating Peace	Explore how power affects interpersonal relationships, community violence, and building strategies to respond
5. Building conflict resolution or upstander skills	Manhood 2.0, Sisterhood 2.0, and Creating Peace	Develop nonviolent communication strategies to manage interpersonal conflict and safely intervene using upstander behaviors
6. Strengthening job skills	Job skills training	Develop workforce skills to promote job readiness: identifying strengths and skills, resumes, letters of reference, and finding employment opportunities
7. Succeeding in the job search	Job skills training	Develop workforce skills to promote job readiness (part II): job applications, interviews, and preparing for work
8. Empowering youth as change agents	Creating Peace	Define and build leadership skills through an empowerment framework, become a community leader, introduce photovoice as a catalyst for change
9. Envisioning a collective future	Creating Peace	Create a collective vision for a safe and supportive community using human-centered design activities
10. Networking for job success	Job skills training	Meet with job readiness programs and community mentoring programs and work with facilitators to identify and connect with employment, mentorship, and leadership opportunities
11. Reflecting and preparing to share	New synergistic content	Preparing presentations, practicing leadership skills, and showcasing visual and written expressions of empowerment
12. Sharing and celebrating with community	New synergistic content	Youth present their project celebrating identity, strengths, and skills to the broader community; graduation from program with community leaders, adult allies, and workforce development program leaders present

Youth in the comparison arm receive an individual wellness check-in (in-person or by phone) with tailored referrals to community resources and optional follow-up. This occurs through a strengths-based conversation focused on wellness resources, conducted by trained community facilitators and staff, typically lasting 20 minutes. Youth are offered the option of additional phone check-ins to coordinate access to community resources and connection to individualized behavioral health supports, if desired.

### Measures

The primary outcome of interest is the change in violence perpetration over the past 3 months, assessed via a self-report composite measure of physical fighting, threatening someone with a weapon, and injuring someone with a weapon at T2 (Table 2). Secondary outcomes focus on violence perpetration (as per the primary outcome measure) measured at 6 months (T3), as well as the change in self-reported use of a range of types of violence in the past 3 months, including relationship abuse, sexual violence, bullying, weapon carrying, homophobic teasing, and sexual harassment.

**Table 2. T2:** Primary and secondary outcome measures.

Outcomes	Measures description	Time frame
Primary outcome		
Change in recent violence perpetration at 3 months	Self-report on 3 items adapted from the Youth Risk Behavior Surveillance Survey, using a past-3 month reporting interval: (1) physical fighting (“How many times were you in a physical fight?“), (2) threatening someone with a weapon (“How many times have you threatened someone with a weapon such as a gun, knife, or club?“), and (3) injuring someone with a weapon (“How many times have you injured someone with a weapon such as a gun, knife, or club?"). Each item will be assessed with 8 frequency response categories from 0 to 12 or more times. A summary score will capture the past 3-month incidence of all 3 behaviors (possible range: 0‐21; lower score indicates better outcome)	At baseline and 3 months after program conclusion
Secondary outcomes		
Change in recent violence perpetration at 6 months	This will be measured using the same 3 items outlined in the primary outcome, but assessed as a change from baseline to 6 months after program conclusion. This includes self-report on 3 items adapted from the Youth Risk Behavior Surveillance Survey, using a past-3 month reporting interval: (1) physical fighting (“How many times were you in a physical fight?“), (2) threatening someone with a weapon (“How many times have you threatened someone with a weapon such as a gun, knife, or club?“), and (3) injuring someone with a weapon (“How many times have you injured someone with a weapon such as a gun, knife, or club?"). Each item will be assessed with 8 frequency response categories from 0 to 12 or more times. A summary score will capture the past 3-month incidence of all 3 behaviors (possible range: 0‐21; lower score indicates better outcome)	At baseline and 6 months after program conclusion
Change in relationship abuse at 3 months	Ten abusive behavior items, modified from Conflict Tactics Scale-2, assess for perpetration against dating partners or toward peers. Summary score of any recent use of violence in the past 3 months (physical, sexual, and emotional relationship abuse) calculated as one point for each behavior then summed (possible range: 0‐10; lower score indicates better outcome).	At baseline and 3 months after program conclusion
Change in sexual violence perpetration at 3 months	Four sexual violence perpetration items assess recent sexual violence perpetration (any or none). Summary score of any recent sexual violence perpetration in the past 3 months, calculated as 1 point for each behavior then summed (possible range: 0‐4; lower score indicates better outcome).	At baseline and 3 months after program conclusion
Change in cyber dating abuse and peer abuse	Eight items assess using technology to perpetrate abuse against a dating partner or peers. Summary score of any recent use of technology to perpetrate abuse against a dating partner or peers in the past 3 months, calculated as 1 point for each behavior then summed (possible range: 0‐8; lower score indicates better outcome).	At baseline and 3 months after program conclusion
Change in bullying perpetration	Three items to indicate frequency of bullying perpetration on 3-point frequency scale. Mean score of any recent bullying perpetration in the past 3 months, calculated as a mean score across the 3 items (possible range: 0‐2; lower score indicates better outcome).	At baseline and 3 months after program conclusion
Change in weapon carrying	One item adapted from the Youth Risk Behavior Surveillance Survey asking about frequency of carrying a weapon in the past 3 months (measured on a 5-point frequency scale from 0 days to 6 or more days; possible range: 0‐4; lower score indicates better outcome).	At baseline and 3 months after program conclusion
Change in homophobic teasing	Five-item scale with participants reporting how often they have perpetrated listed behaviors in the past 3 months (each item measured on a 5-point frequency scale from 0 to 7 or more times). Mean score of recent homophobic teasing, calculated as a mean across the 5 items (possible range: 0‐4; lower score indicates better outcome).	At baseline and 3 months after program conclusion
Change in sexual harassment	Five items assess frequency of perpetrating sexual harassing behaviors in the past 3 months, assessing perpetration frequency on a 4-point frequency scale. Mean score of recent sexual harassment perpetration in the past 3 months, calculated as a mean across the 5 items (possible range: 0‐3; lower score indicated better outcome).	At baseline and 3 months after program conclusion

Intermediate outcomes will assess violence-related attitudes and behaviors, as well as youth empowerment, future orientation, civic engagement, self-efficacy, and other key social variables (eg, gender attitudes) [44] (Figure 3). Prior violence exposure (witnessing and victimization) and neighborhood context will be assessed at T1. Demographics include age, gender, race or ethnicity, and housing or education context.

**Figure 3. F3:**
[figure not shown]
Forging Hopeful Futures intervention components and hypothesized outcomes.

### Data Collection and Procedures

Surveys are administered via secure tablets or web links in private spaces at each time point (T1–T3). To protect confidentiality for sensitive topics, surveys are anonymous and linked across time using a self-generated code derived from stable personal prompts [45]. Research staff provide brief instructions and remain available if technical or literacy support is needed. To enhance retention, the team uses multimodal reminders, flexible scheduling, and community partner touchpoints; incentives are modest and escalate across follow-ups. A subset of FHF youth and facilitators participates in qualitative interviews to contextualize implementation facilitators and barriers.

### Sample Size and Power

In determining the number of neighborhood clusters to include in the study, we sought to balance expected effect sizes with feasibility and budgetary constraints for a 3-year multicity study. Our selection of 16 clusters was informed by a previous cluster-RCT led by our team to evaluate the Manhood 2.0 curriculum and a pilot feasibility study of the Sisterhood 2.0 program (NCT02427061 and NCT04388696, respectively). We used these study findings to guide assumptions for our sample size calculations [34,39,40,46]. Sample sizes for each outcome were based on clinically meaningful differences between treatment groups with respect to changes in outcomes across time (ie, intervention effect). For the primary outcome of self-reported youth violence perpetration (fighting or weapon violence perpetration) in objective 1, the necessary sample size was calculated based on traditional methods that assume a fixed number of clusters. If we assume 8 neighborhoods randomized per arm with a conservative within-site correlation of 0.01, and 20% attrition at 3 months, we need 360 participants per arm (total N=720) to detect a standardized effect size of 0.39 with 80% power. This translates to a 35% relative reduction in the primary outcome, assuming a 57% rate in the control arm at 3 months. For all secondary outcomes, we have similar power to detect a standardized effect size of 0.39.

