### Statistical Analysis

Descriptive statistics will be used to summarize the sample with regard to baseline characteristics of interest. Means and SDs will be presented for continuous variables, while sample proportions will be provided for categorical variables.

Primary assessment of intervention effects will be based on intent-to-treat analyses. As-treated effect parameters will be estimated in secondary, exploratory analyses. We will conduct intervention intensity-adjusted analyses (estimating the dose that participants received) by substituting a score between 0 and 1 for the treatment group. Additionally, we will conduct per-protocol analyses, with participants exposed to “intervention as intended” in the treatment arm and all others treated as controls (ie, 0). Generalized linear mixed models will be used to account for stratification by city, correlation between youth from the same neighborhood, as well as the correlation between longitudinal observations from the same youth. SAS (Statistical Analysis System) software (SAS Institute) will be used for all statistical analyses. All hypotheses will be 2-sided tests with a significance level of 5%, and 95% CIs will accompany all sample statistics.

Participation bias will be assessed by comparing the age and race or ethnicity of youth participating in the study to each neighborhood’s overall demographics of youth (based on census tract data). Attrition analysis will be conducted by comparing youth who completed follow-up surveys with those who did not, based on demographics as well as outcomes measured at baseline. Mechanisms for missing data will be investigated by comparing important covariates between youth with and without missing data at each time point. We will characterize these mechanisms as (1) missing completely at random, (2) missing at random, or (3) not missing at random. If the nature of our missing data is ignorable (either missing completely at random or missing at random), we will use imputation methods, such as multiple imputation via chained equations, to handle dropout. Ultimately, sensitivity analyses will be conducted to compare the results of our imputation methods to complete-case and available-data analyses.

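### The printed sample-size inputs do not give the printed result: with ICC 0.01, 360 per arm detects about 0.27–0.29 at 80% power, not 0.39

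*Protocol article*

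**What the plan says.** The Sample Size and Power section of the protocol article names a conventional method with a fixed number of clusters. Its inputs are "8 neighborhoods randomized per arm with a conservative within-site correlation of 0.01, and 20% attrition at 3 months", and its output is "we need 360 participants per arm (total N=720) to detect a standardized effect size of 0.39 with 80% power". It equates this effect to a 35% relative reduction from a 57% control-arm rate at 3 months, and claims similar power at 0.39 for every secondary outcome.

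The other inputs are elsewhere in the article. Statistical Analysis states: "All hypotheses will be 2-sided tests with a significance level of 5" percent. Study Design and Setting plans "Approximately 45 youth" per neighborhood, which over 16 neighborhoods gives the same 720. Randomization is 1:1 by neighborhood.

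The sizing paragraph also says that the differences of interest concern change over time. It gives no within-youth correlation and does not say whether a normal or a t reference was used.

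**The concern.** The paragraph gives cluster count, ICC, attrition, power, effect and total N together, so a reader can check them against each other. A design effect of 1.35 on 288 completers per arm is mild, and 0.39 is a large effect to need that many youth.

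These figures are what readers will use to judge how small an effect the trial could have found, above all if the result is null. If the ICC of 0.01 applies to a single post-program score, the trial is more sensitive than stated. If the 720 was in fact built on an ICC of 0.04–0.05, the stated ICC is wrong and the 80% has no reserve at that value. Readers would draw different conclusions in the two cases.

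**Working it through.** **Inputs.** k = 8 clusters per arm, ICC = 0.01, 20% attrition, 360 enrolled per arm, 80% power and effect 0.39 (Sample Size and Power); two-sided 5% (Statistical Analysis); 45 enrolled per cluster (Study Design and Setting). Equal cluster sizes are assumed.

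**Attempt to reproduce the plan's figure.**
- Completers per cluster: m = 45 × 0.8 = 36. Per arm: n = 8 × 36 = 288.
- Design effect: 1 + (36 − 1) × 0.01 = 1.35. Effective n per arm: 288 / 1.35 = 213.3.
- SE of the standardized difference: √(2 × 1.35 / 288) = 0.0968.
- Detectable effect, normal: (1.960 + 0.842) × 0.0968 = **0.271**. Noncentral t, 14 df: **0.292**. The plan states 0.39.
- Power at 0.39: 0.39 / 0.0968 = 4.03, and 4.03 − 1.96 = 2.07, so **98.1%** (normal); **96.2%** (t, 14 df). The plan states 80%.

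**N needed for 0.39 at ICC 0.01.** Ignoring clustering, n = 2 × 2.8016² / 0.39² = 103.2, so 104 per arm. The fixed-cluster formula gives m = 104 × 0.99 / (8 − 104 × 0.01) = 14.8, so 15 per cluster, 120 completers and 120 / 0.8 = **150 enrolled per arm**. With t, 14 df, m = 18, giving 144 completers and **180 enrolled per arm**. The plan states 360.

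**Other computational choices, stated inputs kept (normal formula).**

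| Variant | Detectable effect |
|---|---|
| Attrition ignored | 0.251 |
| Design effect at m = 45 | 0.280 |
| One-sided 5% | 0.241 |
| 90% power | 0.314 |

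None reaches 0.39.

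**Binary version.** 57% × 0.65 = 37.05%. The standardized difference is 0.1995 / √(0.47025 × 0.52975) = 0.40, so the 35% and the 0.39 roughly agree. Sizing on these two proportions needs 140 enrolled per arm (160 with continuity correction), and 360 per arm gives 98.7% power. The translation is therefore not the source of the gap.

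**What would reconcile the figures.**
1. *A different ICC.* Normal: (0.39 / 2.8016)² × 288 / 2 = 2.79, so ICC = 1.79 / 35 = 0.051. With t, 14 df: 0.040.
2. *360 as the total.* With 180 enrolled per arm, t with 14 df gives 0.384. However, the 45 per neighborhood and 16 neighborhoods confirm 720 as the enrollment target.
3. *An unstated variance.* A difference in change standardized by the raw SD multiplies the variance by 2(1 − r), where r is the within-youth correlation. At r = 0 the normal formula gives 0.271 × √2 = 0.384 (power at 0.39: 81.3%). At r = 0.1, t with 14 df gives 0.292 × √1.8 = 0.391. At r = 0.3 the range is 0.32–0.35, and at r = 0.5 it is 0.27–0.29.

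**Detectable effect at 80% power by ICC (m = 36, single post-program score).**

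| ICC | Normal | t, 14 df | Power at 0.39, normal |
|---|---|---|---|
| 0.01 | 0.27 | 0.29 | 98% |
| 0.02 | 0.30 | 0.33 | 95% |
| 0.03 | 0.33 | 0.36 | 90% |
| 0.04 | 0.36 | 0.39 | 86% |
| 0.05 | 0.39 | 0.42 | 81% |

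**Relative reduction at ICC 0.01.** Scaling the plan's own pairing of 0.39 with 35%: 35% × 0.271 / 0.39 = 24%, and 35% × 0.292 / 0.39 = 26%.

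**The case against.** The strongest reply is that every printed figure could be right. The sizing paragraph speaks of change over time and the Measures section defines the primary outcome as a change, so the calculation may have used a change-score variance with an r that a condensed article does not print. With r near zero this roughly gives 0.39 at ICC 0.01. The reply stands to this extent: the document does not exclude the route, so it cannot be said that a figure must be wrong. The route needs r of about 0 to 0.1, which sits badly with the plan to model correlation between repeated observations on the same youth. The 57% and 35% translation also compares 3-month rates, not changes.

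A reader might go further and infer that 0.01 has been shown not to be conservative, or that 0.39 holds only at an ICC of about 0.04. Neither is supported. The basis for 0.01 lies in prior studies that are not at hand, 0.051 under the normal formula fits as well as 0.040 under t, and the change-score route leaves 0.01 intact. Nor is the trial shown to be underpowered: at face value the printed inputs give more power than claimed.

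It can also be said that the limitations already warn that correlations and effect sizes may differ, and that confidence intervals will accompany the results. Both are true. Neither tells a reader which planning assumption was used. This is also not a detail left to a fuller document, because the article prints its inputs beside an output that they do not produce.

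**Conclusion.** The sample-size statement is wrong as written, because its output does not follow from its printed inputs. The gap is too large for rounding or choice of test: a detectable effect of 0.27–0.29 against 0.39, power of 96–98% against 80%, and 150–180 enrolled per arm against 360, an overstatement of 2 to 2.4 times. Either a printed figure is wrong or a decisive input is unstated, and the document does not show which.

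The result rests on equal cluster sizes, 36 completers per neighborhood, two-sided 5% and a standardized difference on a single post-program score. The arithmetic is firm under those assumptions. The explanation for the gap is open.

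**What to change.** Correct the paragraph so that inputs and output agree:
- State the ICC, the variance or within-youth correlation, and the reference distribution actually used.
- Restate the matching detectable effect and relative reduction. If ICC 0.01 on a single post-program score was intended, these are about 0.27–0.29 and roughly 24–26%. Otherwise correct the ICC or state the missing variance input.
- Carry the correction into the sentence on power for secondary outcomes.
- Add a short table of detectable effect for ICC 0.01 to 0.05 (normal formula: 0.27, 0.30, 0.33, 0.36, 0.39).
- Keep the description of the ICC as conservative only if the value actually used supports it.

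The answer has to come from the planning records, since data collected so far cannot show which inputs were used. The cost is one paragraph and a small table. Enrollment, randomization, follow-up and analysis are unaffected, and the correction can be made before the primary analysis expected on January 1, 2027.

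### The 57% rate and 35% reduction used to explain the power calculation describe a yes/no outcome, but the primary outcome is change in a 0–21 score

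*Protocol article*

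**What the plan says.** Under Measures, Table 2 builds the primary outcome from three items on fighting, threatening with a weapon and injuring with a weapon. On the items: "Each item will be assessed with 8 frequency response categories from 0 to 12 or more times". On their combination: "A summary score will capture the past 3-month incidence of all 3 behaviors", with "possible range: 0‐21; lower score indicates better outcome". The outcome is the change in this score from baseline to 3 months after the program.

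Sample Size and Power introduces the calculation with these words: "For the primary outcome of self-reported youth violence perpetration (fighting or weapon violence perpetration) in objective 1". It assumes "8 neighborhoods randomized per arm with a conservative within-site correlation of 0.01, and 20% attrition at 3 months" and concludes: "we need 360 participants per arm (total N=720) to detect a standardized effect size of 0.39 with 80% power". It then gives the effect a concrete meaning: "This translates to a 35% relative reduction in the primary outcome, assuming a 57% rate in the control arm at 3 months". The section ends: "For all secondary outcomes, we have similar power to detect a standardized effect size of 0.39".

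Statistical Analysis names a generalized linear mixed model without a distribution or link. The Results paragraph of the Abstract adds adjustment for baseline values and city.

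**The concern.** The two sections describe the primary outcome on different scales. Eight categories per item, coded 0 to 7, give a maximum of 3 × 7 = 21, so Table 2 is consistent with itself and clearly means a frequency score. A rate in the control arm belongs to a yes/no outcome. The article nowhere defines a yes/no version of the primary outcome, gives a mean or SD for the score, or says how the two scales relate.

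The 57%/35% sentence is the only place where the article says what an effect of 0.39 would mean in practice. If it describes a different variable, a reader cannot tell what size of benefit on the analysed endpoint the trial can detect. The secondary outcomes have a similar gap. They are counts (0–10, 0–4, 0–8), item means and a single 0–4 frequency item, and one figure of 0.39 says nothing about the detectable change on any of them.

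**Working it through.** **Inputs from the article.** Control rate 57%; relative reduction 35%; standardized effect 0.39; power 80%; 360 enrolled per arm; 8 clusters per arm; ICC 0.01; 20% attrition; two-sided 5%.

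**Step 1: where 0.39 fits.**
- FHF rate: 0.57 × (1 − 0.35) = 0.3705.
- Cohen's h = 2·arcsin(√0.57) − 2·arcsin(√0.3705) = 0.402.
- Difference over pooled SD: the average rate is 0.47025, so 0.1995 / √(0.47025 × 0.52975) = 0.400.
- In reverse, h = 0.39 from 57% is a 34% relative reduction.

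The 57%/35% sentence therefore agrees with 0.39, to rounding, when the outcome is any-versus-none.

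**Step 2: information in the planned sample.**
- Analysed per arm: 360 × 0.8 = 288, or 36 per cluster.
- Design effect: 1 + 35 × 0.01 = 1.35.
- Effective n per arm: 288 / 1.35 = 213.3.
- Effect detectable with 80% power: (1.96 + 0.84) × √(2/213.3) = 0.27 (normal), or 0.29 (t, 14 df).

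On these inputs, power for 0.39 is 98% (normal) or 96% (t), not 80%. That the stated inputs do not return 360 per arm is a separate matter and is not used below.

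**Step 3: the same 35% on the score (illustration only).** The article gives no distribution, so these are assumptions:
- 57% of control youth score above zero.
- Positive scores follow a truncated geometric shape, proportional to r^(x−1) for x = 1 to 21, with r from 0.5 to 0.8.
- FHF acts only by lowering the share above zero to 37.05%.
- There is no baseline adjustment.

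With positive-part mean μ and second moment q, the arm mean is pμ, the variance is pq − (pμ)², and d is the difference in means over the root of the average variance.

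For r = 0.5, μ = 2.00 and q = 6.00:
- Control: mean 1.14, variance 3.42 − 1.30 = 2.12.
- FHF: mean 0.741, variance 2.223 − 0.549 = 1.674.
- d = 0.399 / √1.897 = 0.290.

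| r | Control mean (SD) | d | Power, normal | Power, t (14 df) |
|---|---|---|---|---|
| 0.5 | 1.14 (1.46) | 0.290 | 85% | 79% |
| 0.6 | 1.42 (1.91) | 0.276 | 81% | 76% |
| 0.7 | 1.89 (2.65) | 0.267 | 79% | 73% |
| 0.8 | 2.74 (3.83) | 0.266 | 78% | 72% |

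In this model the mean score also falls by 35%, yet d is below 0.39. With no spread among positive scores, d is 0.408, the yes/no value. Spread among perpetrators lowers it.

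**Step 4: dependence on the assumed shape.** If only the coefficient of variation (CV) of positive scores is specified, at 0.5, 1.0 or 1.5, d is 0.33, 0.24 or 0.18 and normal-theory power is 93%, 69% or 44%. The answer depends on a distribution that the article does not give.

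**The case against.** The strongest reply is that the calculation is stated for a standardized effect, which is scale-free. An effect of 0.39 can apply to a score as well as to a proportion, and the 57% sentence only translates it. That stands. A reader might infer that the stated power belongs to a binary endpoint and that the trial is underpowered for the score. The article supports neither. The binary origin of 0.39 is a close numerical match, not something the article states.

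The illustration is also one-sided. It lets FHF change whether youth perpetrate but not how often, and it leaves out the planned baseline adjustment. With an assumed baseline correlation of 0.5, d is divided by √(1 − 0.25) and becomes 0.31–0.33, with power of 84–89% (t) or 89–93% (normal). If r also falls by 10% among FHF perpetrators, d becomes 0.36–0.44. That is a larger total effect, but it shows that 0.39 is attainable on the score. Even without these allowances, the illustrated power lies on both sides of 80%.

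A reader might also apply national prevalence figures to the secondary outcomes and infer that 0.39 would require near-elimination of rare behaviors. That does not follow. Those outcomes are counts and frequency scores, and the Introduction's weapon-carrying figure is a national 30-day rate, not a 3-month rate in these neighborhoods.

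Finally, the model's distribution and link may properly sit in an analysis plan not shown here. That is accepted, and their absence is not the complaint. The complaint is that two statements in the article do not describe the same variable. A binary model would remove the mismatch with the power section only by contradicting Table 2.

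**Conclusion.** The point holds as an inconsistency between the power justification and the endpoint definition. The 35% reduction from 57% describes any-versus-none perpetration and is unsupported for change in the 0–21 score. The mismatch itself rests on the article's text and on the arithmetic for 57% against 37.05%, and needs no assumption.

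Its effect on power is uncertain. Under the truncated geometric illustration, d is about 0.27–0.29 and power is about 72–79% (t, 14 df) or 78–85% (normal) at ICC 0.01. Other shapes, baseline adjustment or a change in frequency among perpetrators move these figures in either direction. It is not shown that 720 is too small. What is shown is that the article does not say what benefit on its own primary endpoint the trial can detect. This should be corrected before the primary analysis.

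**What to change.** Keep the 0–21 score as primary.

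1. Replace the 57%/35% sentence with the detectable difference, or ratio, of mean scores. Compute it from the mean, SD and share of zeros in the pooled, arm-blind T1 data, allow for the planned baseline adjustment, and show a range for the assumed baseline-to-follow-up correlation.
2. If any-versus-none is of interest, report it only as a supportive analysis with its own 57%-to-37% power statement.
3. Replace the blanket 0.39 sentence with the detectable difference on each secondary outcome's own scale, from the same blinded data.

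The cost is a recalculation and new wording. Recruitment, data collection and the primary endpoint do not change. The article reports 542 youth enrolled by December 1, 2025 and expects the primary analysis on January 1, 2027, so baseline data are available in time and arm labels need not be opened. The restated power may look less favorable than the current sentence.
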